## Abstract

**Background:**

Periprosthetic joint infection (PJI) is a challenging complication following total joint arthroplasty (TJA), and the diagnostic criteria remains controversial. The 2018 new definition proposed in May 2018 consists of new diagnostic criteria for PJI. We conducted a retrospective study and demonstrated that the new definition could improve the diagnostic efficiency in Chinese patients. However, missing data led to bias in the previous retrospective study. Therefore, this prospective study is designed to further validate the feasibility of 2018 new definition (and its modified version) for Chinese patients.

**Methods/design:**

This is a single-centre, prospective diagnostic study with 1 year of follow-up. The patients enrolled in the trial will be divided into a PJI group and an Aseptic group based on the eligibility criteria. We will recruit at least 70 patients for each group from October 2019 to October 2020. Blood samples, synovial fluid samples and intraoperative variables of all the included patients will be collected to assess various indicators. We will integrate the results of the various tests and examine the diagnostic efficiency (sensitivity and specificity) of five diagnostic criteria.

**Discussion:**

We design the prospective study in the hope of reducing the bias caused by missing data. Therefore, the prospective study will further support the conclusion of our preceding retrospective study. The results of this study will be submitted to a peer-reviewed journal for publication.

**Conclusion:**

Through this prospective study, we will validate the feasibility of the 2018 new PJI definition (and its modified version) for Chinese patients and determine the optimal method of PJI diagnosis.

**Trial registration:**

Chinese Clinical Trial Registry, ChiCTR1900025395. Registered on 25 August 2019.

## Background

With the rapid growth of the ageing population, the number of patients requiring total joint arthroplasty (TJA) for the treatment of osteoarthritis or other degenerative joint diseases has been rapidly increasing [1–4]. Periprosthetic joint infection (PJI) is the most devastating postoperative complication and is harmful to the health and economic status of patients [5–8]. Although strict aseptic techniques and rational antibiotic management after surgery are widely followed in clinical practice, PJI is still common in patients undergoing failed TJA [8]. It has been reported that 20.4% of patients undergo revision total knee arthroplasty (TKA) due to PJI in the United States [9].

The diagnosis of PJI is still controversial, and orthopaedic surgeons are searching for a more accurate diagnostic method that could help in determining whether revision surgery is appropriate for patients. At present, the diagnostic criteria proposed by the Musculoskeletal Infection Society (MSIS) and then partly modified at the International Consensus Meeting (ICM) in 2013 is widely used in the diagnosis of PJI [10–12]. Due to the advances in the knowledge of orthopaedic surgeons regarding PJI and the development of the means of detection, it is necessary to further improve the diagnostic efficiency of the MSIS and ICM criteria. In 2018, researchers proposed a new definition of PJI by establishing an evidence-based and weight-adjusted scoring system [13]. The scoring system involved intraoperative variables, preoperative serum markers and synovial markers. Researchers evaluated the new definition on a total of 422 patients and concluded that the new definition provided better sensitivity and similar specificity compared with the MSIS and ICM criteria [13]. The new definition was reviewed and further altered by the International Consensus on Orthopedic Infections [14].

To validate the feasibility of the new PJI definition for Chinese patients, we retrospectively studied a cohort of 98 patients in a PJI group and 165 patients in an aseptic loosening group [15]. The included patients all underwent revision total knee (TKA) and hip arthroplasty (THA) between January 2015 and August 2017 in our hospital. For patients in both groups, the sensitivity of the new PJI definition reached 94.9%, which was significantly higher than that of the MSIS and ICM criteria. The specificity of the new definition remained at 95.2%. Therefore, we concluded that the 2018 new definition of PJI was also appropriate for use with Chinese patients [15].

However, in the retrospective study, part of the data were lost due to the loss of medical records, and some synovial markers were not available because they are not widely measured in clinical practice. To reduce the bias caused by these missing data and to improve the quality of our research, we designed and planned to conduct a prospective study that could further validate the feasibility of the new PJI definition for Chinese patients.

## Methods

### Study design and objectives

This single-centre trial is designed as a prospective diagnostic study. The objectives of this study are to supplement and improve the results of the preceding prospective study and to validate the feasibility of the 2018 new PJI definition for Chinese patients. The study is nonrandomized, and all patients serve as their own controls. From October 2019 to October 2020, we will recruit patients who agree to participate in the trial in the Department of Orthopaedics of the Chinese PLA General Hospital (301 hospital). Blood samples, synovial fluid samples and intraoperative findings will be collected for patients meeting the inclusion criteria. All of the samples and clinical data will be processed and analysed by a double-blind method. The major criteria of PJI (a sinus tract communicating with the joint or two positive cultures of the same organism) are identical among various diagnostic criteria [10–14, 16]. Therefore, we will use the major criteria as the gold standard to divide the enrolled patients into a PJI group and an Aseptic group. Then, we will compare the diagnostic efficiency of the respective minor criteria among the 2018 new definition (before revision and after revision), the MSIS criteria, the ICM criteria and the IDSA (Infectious Diseases Society) criteria (Tables 1, 2, 3, 4 and 5) [10–14, 16]. All patients included in our study will be followed for at least 1 year.

**Table 1 Tab1:** New scoring based definition for periprosthetic joint infection (PJI)

Major criteria (at least one of the following)				Decision
Two positive cultures of the same organism				Infected
Sinus tract with evidence of communication to the joint or visualization of the prosthesis				
Preoperative Diagnosis	Minor criteria		Score	Decision
	Serum	Elevated CRP or D-Dimer	2	≥6 Infected 2–5 Possibly Infected^a^ 0–1 Not Infected
		Elevated ESR	1	
	Synovial	Elevated Synovial WBC or LE	3	
		Positive Alpha-defensin	3	
		Elevated Synovial PMN (%)	2	
		Elevated Synovial CRP	1	
Intraoperative Diagnosis	^a^Inconclusive pre-op score or dry tap		Score	Decision
	Preoperative Score		–	≥6 Infected 4–5 Inconclusive^b^ ≤3 Not Infected
	Positive Histology		3	
	Positive Purulence		3	
	Single Positive Culture		2	

Proceed with caution in: Adverse local tissue reaction, crystal deposition disease, slow growing organisms

^a^For patients with inconclusive minor criteria, operative criteria can also be used to fulfill definition for PJI

^b^Consider further molecular diagnostics such as next-generation sequencing

**Table 2 Tab2:** Proposed 2018 ICM criteria for PJI (modified version of the 2018 new definition)

Major criteria (at least one of the following)				Decision
Two positive growth of the same organism using standard culture methods				Infected
Sinus tract with evidence of communication to the joint or visualization of the prosthesis				
Minor Criteria	Threshold		Score	Decision
	Acute^b^	Chronic		Combined preoperative and postoperative score: ≥6 Infected 3–5 Inconclusive^a^ <3 Not Infected
Elevated CRP (mg/L)	100	10	2	
or				
D-Dimer (ug/L)	Unknown	860		
Elevated Serum ESR (mm/hr)	No role	30	1	
Elevated Synovial WBC (cells/μL)	10,000	3000	3	
or				
Leukocyte Esterase	++	++		
Or				
Positive Alpha-defensin (signal/cutoff)	1.0	1.0		
Elevated Synovial PMN (%)	90	70	2	
Single Positive Culture			2	
Positive Histology			3	
Positive Intraoperative Purulence^c^			3	

^a^Consider further molecular diagnostics such as Next-Generation Sequencing

^b^These criteria were never validated on acute infections

^c^No role in suspected adverse local issue reaction

**Table 3 Tab3:** Musculoskeletal Infection Society (MSIS) criteria proposed in 2011

Major criteria	
1. There is a sinus tract communicating with the prosthesis	
2. A pathogen is isolated by culture from at least two separate tissue or fluid samples obtained from the affected prosthetic joint	
Minor criteria	
1. Elevated serum erythrocyte sedimentation rate (ESR) and serum C-reactive protein (CRP) concentration	
2. Elevated synovial leukocyte count	
3. Elevated synovial neutrophil percentage (PMN%)	
4. Presence of purulence in the affected joint	
5. Isolation of a microorganism in one culture of periprosthetic tissue or fluid	
6. Greater than five neutrophils per high-power field in five high-power fields observed from histologic analysis of periprosthetic tissue at× 400 magnification.	

PJI exists when one of the major criteria occurs or four of the six minor criteria occur

**Table 4 Tab4:** International Consensus Meeting (ICM) criteria proposed in 2013

Major criteria	
1. Two positive periprosthetic cultures with phenotypically identical organisms	
2. A sinus tract communicating with the joint	
Minor Criteria	
1. Elevated serum C-reactive protein (CRP) and erythrocyte sedimentation rate (ESR)	
2. A single positive culture	
3. Elevated synovial fluid white blood cell (WBC) count or ++ change on leukocyte esterase test strip	
4. Elevated synovial fluid polymorphonuclear neutrophil percentage (PMN%)	
5. Positive histological analysis of periprosthetic tissue	

PJI exists when one of the major criteria occurs or three of the five minor criteria occur

**Table 5 Tab5:** Infectious Diseases Society of America (IDSA) criteria

Definition of PJI	
1. The presence of a sinus tract that communicates with the prosthesis 2. The presence of acute inflammation based on histopathologic examination of periprosthetic tissue at the time of surgical debridement or prosthesis removal. 3. The presence of purulence surrounding the prosthesis. 4. Two or more intraoperative cultures or combination of preoperative aspiration and intraoperative cultures that yield the same organism. Growth of a virulent microorganism (eg, *S. aureus*) in a single specimen of a tissue biopsy or synovial fluid may also represent PJI. 5. The presence of PJI is possible even if the above criteria are not met; the clinician should use his/her clinical judgment to determine if this is the case after reviewing all the available preoperative and intraoperative information	

### Primary outcome

The diagnostic efficiency (sensitivity) of PJI with the minor criteria of the 2018 new definition (before and after revision).

### Secondary outcomes

The following will be assessed:

Specificity, true positive, true negative, false positive, false negative, positive predictive value and negative predictive value of the new definition (before and after revision).

Sensitivity, specificity, true positive, true negative, false positive, false negative, positive predictive value and negative predictive value of the MSIS criteria.

Sensitivity, specificity, true positive, true negative, false positive, false negative, positive predictive value and negative predictive value of the ICM criteria.

Sensitivity, specificity, true positive, true negative, false positive, false negative, positive predictive value and negative predictive value of the IDSA criteria.

The outcomes above are calculated from the data of patients’ medical record information and laboratory tests. We would like to summarize these outcome data as follows. Patients’ basic information such as demographics, comorbidities and surgery information will be collected first through reviewing patients’ medical records or asking patients themselves. Then we will collect data of serum indicators, synovial indicators and intraoperative indicators of each patient. Serum indicators consist of serum C-reactive protein (CRP), serum D-Dimer, serum interleukin-6 (IL-6) and erythrocyte sedimentation rate (ESR). Synovial indicators consist of synovial white blood cell (WBC), leukocyte esterase (LE), synovial alpha-defensin, synovial polymorphonuclear neutrophil percentage (PMN%) and synovial CRP. Intraoperative indicators consist of histology (pathological data from freezing tissue slices), existence of purulence and microorganism culture. These outcome data will be used to determine whether PJI occurs according to various criteria. Finally, we will acquire result of sensitivity, specificity, true positive, true negative, false positive, false negative, positive predictive value and negative predictive value of five diagnostic criteria of PJI. The concrete methods of data acquisition and processing are clearly introduced in the subsequent ‘Recruitment and intervention’ section.

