### Sample size

Sample size calculations were performed using PASS software version 19.0.2 (licensed by NCSS, LLC). In our retrospective study, the sensitivity and specificity of the new definition were 94.9% (95% confidence interval [CI] 87.9–98.1%) and 95.2% (95% CI 90.3–97.7%), respectively [15]. Based on the results of our calculation, we should analyse the data of 60 patients in the PJI group and 58 patients in the Aseptic group. Therefore, we need to include at least 63 patients in the PJI group and 61 patients in the Aseptic group under the assumption of 5% withdrawal and loss to follow-up. In case some patients are excluded from the study for other clinical reasons, we decided to include at least 70 patients in each group.

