### Statistical analysis

The statistical analysis will be carried out with IBM SPSS statistics version 20 (SPSS Inc., Armonk, NY). Descriptive statistics will be determined as numbers (frequencies), medians (lower quartile, upper quartile) and means ± standard deviations. Differences in demographic characteristics will be analysed with the Chi-square test or Student’s t-test. Statistical significance will be defined as a *p* value < 0.05. We will calculate the true positive, true negative, false positive, false negative, positive predictive value and negative predictive value of the various criteria and finally obtain the sensitivity and specificity results.

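### PPV and NPV are secondary outcomes for all five criteria, but the PJI share they would be computed at comes from recruitment to two separate group targets (about 50% at the minimums) and is not a prevalence

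*Protocol article*

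**What the plan says.** The Secondary outcomes section of the Protocol article names "positive predictive value and negative predictive value of the new definition (before and after revision"), then repeats the list, with sensitivity added, for the MSIS, ICM and IDSA criteria. The Statistical analysis section says the investigators will calculate the true and false positives and negatives together with the predictive values ("false negative, positive predictive value and negative predictive value of the various criteria"). Neither section names a target prevalence, a reweighting or a caveat.

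The case mix is determined elsewhere:

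- **Inclusion criteria.** The PJI group is defined by the major criteria. The Aseptic group is defined by one-stage revision for aseptic reasons.
- **Sample size.** Each group has its own calculated size: "we should analyse the data of 60 patients in the PJI group and 58 patients in the Aseptic group". These become 63 and 61 after an allowance for loss, and finally "we decided to include at least 70 patients in each group".
- **Exclusion criteria and Discussion.** Patients whose synovial fluid cannot be obtained are excluded. The Discussion says this affects the Aseptic group in particular, and that recruitment will be extended if samples run short.

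The Background gives two figures for the share of PJI among revisions. One is a cited report that "20.4% of patients undergo revision total knee arthroplasty (TKA) due to PJI in the United States". The other is the centre's own retrospective cohort of 98 PJI and 165 aseptic loosening patients.

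**The concern.** Sensitivity and specificity are calculated within infected and uninfected patients separately, so the ratio of the two groups does not enter. PPV and NPV mix the groups, so their values depend on the proportion with PJI. Taken from raw counts, they describe patients in practice only if the sample contains PJI in the same proportion as those patients.

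Nothing in the article ties the enrolled proportion to the revision population. Consecutive enrolment is not stated, each group has its own entry rule and target, and one exclusion removes mainly aseptic patients. The proportion is produced by recruitment.

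Readers will take a reported PPV as the chance that a patient who meets the criteria is infected. The study aims to validate the new definition for Chinese patients and to identify the best method of diagnosis, so these figures are likely to be quoted on their own.

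**Working it through.** **Inputs**

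- Sensitivity Se = 0.949 and specificity Sp = 0.952, the planning values for the new definition (Sample size). Their lower 95% limits are 0.879 and 0.903.
- Group sizes of 60/58, 63/61 and at least 70/70 (Sample size).
- PJI share of 98/(98 + 165) = 98/263 = 37.3% (Background, retrospective cohort).
- PJI share of 20.4% (Background, US knee revisions).

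**Step 1: the plan's own sizes.** The inflation for loss reproduces as 60 × 1.05 = 63 and 58 × 1.05 = 60.9, rounded to 61. The article states no precision target. An exact two-sided 95% interval of total width 0.13 gives n = 60 at 94.9% and n = 58 at 95.2%. That width is back-solved, so it is an assumption. It fits the reading that each group was sized separately for its own proportion.

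The PJI share is 60/118 = 50.8% at the analysable sizes, 63/124 = 50.8% after inflation, and 70/140 = 50% at the final minimums. At the cohort ratio of 98:165, 70 PJI patients would come with 70 × 165/98 ≈ 118 aseptic patients. At 20.4% they would come with 70 × 0.796/0.204 ≈ 273.

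**Step 2: predictive values at PJI share p**

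PPV = Se·p / [Se·p + (1 − Sp)(1 − p)]

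NPV = Sp(1 − p) / [Sp(1 − p) + (1 − Se)p]

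- p = 0.50: PPV = 0.949/(0.949 + 0.048) = 0.952; NPV = 0.952/(0.952 + 0.051) = 0.949.
- p = 98/263: PPV = 0.3536/(0.3536 + 0.0301) = 0.922; NPV = 0.5973/(0.5973 + 0.0190) = 0.969.
- p = 0.204: PPV = 0.1936/(0.1936 + 0.0382) = 0.835; NPV = 0.7578/(0.7578 + 0.0104) = 0.986.

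| PJI share | PPV | NPV | False positives among positives |
|---|---|---|---|
| 50% | 95.2% | 94.9% | 4.8% |
| 37.3% | 92.2% | 96.9% | 7.8% |
| 20.4% | 83.5% | 98.6% | 16.5% |

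The crude PPV at 50% is about 3 points above the value at the centre's earlier mix and about 12 points above the value at 20.4%. NPV errs the other way, by about 2 and 4 points.

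**Step 3: sensitivity to the planning values.** At Se = 0.879 and Sp = 0.903, PPV is 90.1% at 50%, 84.3% at 37.3% and 69.9% at 20.4%.

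**Step 4: dependence on recruitment alone.** Hold Se and Sp at the planning values and change only the numbers enrolled. With 70 PJI and 100 aseptic patients (41.2% PJI), crude PPV is 93.3% and NPV 96.4%. With 100 and 70 (58.8% PJI), they are 96.6% and 92.9%. The criteria perform identically in both cases, yet the reported values differ.

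**The case against.** **The 50% is not fixed.** The sizes are minimums, with no cap and no rule closing a group when it is full. The Study design section describes recruiting over a calendar period and then dividing enrolled patients by the major criteria. The Recruitment and intervention section moves an aseptic patient to the PJI group if intraoperative cultures require it. A reader might infer either that 50% is imposed by design or that this is one natural stream of revisions. The documents establish neither. Fifty per cent is the share at the minimums and the achieved share may differ. The single-stream reading also fails, because consecutive enrolment is not stated and the synovial-fluid exclusion would distort the mix anyway.

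**The benchmarks are not this population's prevalence.** This stands. The 20.4% is a US figure for knees only, whereas the centre's cohort included hips and knees. The 37.3% is the ratio of two groups in a retrospective study not stated to be consecutive or to cover all revisions. Both are illustrations.

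**The effect may be small.** At the centre's own earlier mix the PPV shift is 3 points. With about 70 positive results, the approximate 95% half-width is 1.96 × √(0.952 × 0.048/70) ≈ 5 points. That is correct, but the shift is systematic and does not shrink as the sample grows.

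**The main comparisons survive, and readers can correct the values.** This also stands. The primary outcome does not depend on the group ratio. All five criteria are applied to the same patients, so their ranking by PPV or NPV is the same at any common prevalence. The counts are to be reported, so adjusted values can be derived. That limits the harm but does not justify publishing unlabelled crude values.

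**The calculation may be specified elsewhere.** The Statistical analysis section gives no formula, and an analysis plan not shown might add a prevalence. Raw counts are nevertheless the natural reading of what the article states.

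**Conclusion.** The point holds. As described, PPV and NPV for all five criteria would reflect the recruited mix, about 50% PJI at the minimums. Crude PPV is too high and crude NPV too low for any population with less than 50% PJI. On the planning values, PPV is overstated by about 3 points against the centre's earlier mix and by about 12 against the cited US knee figure. NPV is understated by about 2 and 4 points.

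These sizes assume that the retrospective sensitivity and specificity are realised and stay constant across prevalences, and that the achieved mix is close to the minimums. The true PJI share among the patients concerned is not given, so the range matters more than any single figure.

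A reader might conclude that the predictive values are wrong for every clinical population. The documents do not support that, because the values would be about right wherever PJI is near 50%. Nor does the problem reach sensitivity or specificity. It concerns secondary outcomes and can be repaired at the analysis stage. It should be fixed, but the study does not depend on it.

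**What to change.** In the Statistical analysis section, replace predictive values taken from raw group counts with a statement along these lines: PPV and NPV of each criterion will be calculated by Bayes' theorem from its estimated sensitivity and specificity, with 95% confidence intervals, over a stated range of prevalences. The range could run from 20% to 37%, or use the PJI share among consecutive revisions at the centre. State the assumption that sensitivity and specificity carry over from the selected groups to that population. If crude values are also shown, label them as specific to the sample mix and give the achieved group sizes beside them.

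The change takes a few lines. Using cited prevalences needs no new data. Using the centre's own share needs a count of consecutive revisions, and the uncertainty in that share should then be carried into the intervals. The price is a less favourable PPV: 92.2% or 83.5% instead of 95.2% on the planning values.

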### Inclusion criteria

Patients who meet the major criteria of the new definition, that is, patients who have a sinus tract communicating with the joint or two positive cultures of the same organism in tissue or synovial fluid, will be included in the PJI group.Patients who undergo a one-stage revision surgery for aseptic reasons (with no evidence of sinus tracts or two identical positive cultures) will be included in the Aseptic group.

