**Fig. 1 Fig1:**
[figure not shown]
Study flow diagram. The process of recruitment, intervention, follow-ups, data collecting and statistical analysis in our study is presented. PJI = periprosthetic joint infection

A venous blood sample and synovial fluid sample will be obtained from the patients before surgery. After admission, a blood sample will be extracted by a nurse and immediately tested by the Clinical Laboratory of our hospital. The serum CRP, serum IL-6, serum D-Dimer levels and ESR will be determined. Generally, synovial fluid samples will be extracted from PJI patients by an experienced resident physician before admission. Portions of the extracted synovial fluid will be sent to the Division of Microbiology for the culture of microorganisms and to the Clinical Laboratory for routine synovial tests. Therefore, we will acquire the culture results, drug sensitivity results, synovial WBC counts and synovial PMN% when patients visit the hospital. The remaining synovial fluid will be centrifuged and stored in a − 80 C freezer for further study [17]. A drop of centrifuged synovial fluid will be obtained to examine LE [18] (Fig. 2). Importantly, we will not preoperatively extract synovial fluid from patients in the Aseptic group to prevent iatrogenic infection. Therefore, we will not take the culture results before surgery into account when patients are included in the Aseptic group. If two positive cultures of an identical organism are found intraoperatively for a patient in the Aseptic group, the patient will be excluded from the Aseptic group and included in the PJI group instead.

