### Blind reading of outcomes

The information of patients in our study will be accessible to the surgeon responsible for numbering and including patients, the investigator managing synovial fluid samples and the investigator collecting the test results. The results of objective indicators, including demographic characteristics, serum CRP, serum IL-6, serum D-Dimer, ESR, culture results (tissue or synovial fluid), drug sensitivity, histological analysis, synovial white blood cell (WBC) counts and synovial polymorphonuclear neutrophil percentage (PMN%), will be directly recorded by the investigator collecting test results.

The remaining indicators will be first processed and evaluated by an investigator blinded to the details of the patients and samples. Changes on the leukocyte esterase (LE) test strips will be evaluated by an investigator without knowledge of patient information. Synovial alpha-defensin and synovial CRP will be measured by an investigator who obtains only the samples and sample numbers. However, the presence of purulence will be determined by the surgeons who are in control of patient information. These processed data will be collected by the investigator who subsequently collects the test results.

The investigator responsible for statistical analysis will also be blinded to patient information. Nevertheless, it is impossible for the surgeons and resident physicians who extract synovial fluid to be blinded.

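### The cultures that place patients in the PJI group also score a minor item in Tables 1–4, so the sensitivities carry incorporation bias of unequal size across criteria

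*Protocol article*

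**What the plan says.** **Reference standard.** Under Study design and objectives, the Protocol article says "we will use the major criteria as the gold standard to divide the enrolled patients into a PJI group and an Aseptic group". Inclusion criteria define the PJI group as "patients who have a sinus tract communicating with the joint or two positive cultures of the same organism in tissue or synovial fluid" and the Aseptic group as one-stage revisions for aseptic reasons "with no evidence of sinus tracts or two identical positive cultures". Recruitment and intervention adds a reassignment rule: "If two positive cultures of an identical organism are found intraoperatively for a patient in the Aseptic group", that patient moves to the PJI group. Intraoperative cultures are thus part of the reference standard.

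**Index tests.** The tests compared are the minor criteria. The primary outcome is the sensitivity of the minor criteria of the 2018 definition, before and after revision. Secondary outcomes lists microorganism culture among the intraoperative indicators used to apply each set of criteria. Tables 1 and 2 give 2 points to "Single Positive Culture". Table 3 (MSIS) counts "Isolation of a microorganism in one culture of periprosthetic tissue or fluid" as one item, and Table 4 (ICM 2013) has an equivalent item.

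The article does not say whether the group-defining cultures are left out of this item, or whether single means at least one or exactly one.

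**Blinding.** Study design and objectives says "All of the samples and clinical data will be processed and analysed by a double-blind method". Blind reading of outcomes says "the presence of purulence will be determined by the surgeons who are in control of patient information".

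**The concern.** An index test should not be scored from the result that decided the patient's true status. Here the same cultures do both jobs. In a patient who entered the PJI group on two positive cultures, the culture item carries no independent information, yet it supplies a quarter to a third of what each rule needs for a positive call.

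The primary sensitivity is then not that of minor criteria judged independently of the reference standard. Because the item carries different weight in each rule, the differences between criteria are affected too, and the article's Conclusion promises to identify the best diagnostic method.

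A smaller, related matter is purulence. It is worth 3 points in both 2018 versions, is one item in MSIS and one in IDSA, and is absent from ICM 2013. It is recorded by surgeons who know the patient's details, so any observer bias would also be unequal across criteria.

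**Working it through.** **1. The plan's own figures.** The article gives no figure for the overlap. Its planning sensitivity, 94.9%, matches 93/98 in the retrospective PJI group. The 60 PJI patients to be analysed equal the smallest n at which an exact two-sided 95% interval at 94.9% has total width of at most 0.13; that width is inferred, not stated. At n = 60 the interval is about 85.9% to 98.9%. Expected missed cases are 60 × 0.051 ≈ 3.

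**2. Weight of the culture item (Tables 1–4).**

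| Criteria | Needed | Culture item | Share |
|---|---|---|---|
| 2018 definition | 6 points | 2 points | 33% |
| Revised 2018 | 6 points | 2 points | 33% |
| MSIS | 4 items | 1 item | 25% |
| ICM 2013 | 3 items | 1 item | 33% |

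In Table 1, culture counts only after an inconclusive pre-operative score (2–5) or a dry tap. In Table 2 it always counts.

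**3. Who is fixed.** PJI entered on two cultures: always scored (at least one) or never scored (exactly one). PJI entered on a sinus tract alone: cultures can vary. Aseptic: none or one positive culture is possible.

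**4. A hand check.** Assume each other component is independently positive with probability s = 0.7 in PJI. ICM 2013's first item needs both CRP and ESR, so its probability is 0.7² = 0.49; the other three non-culture items have 0.7 each.

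- Item forced on, so 2 of the remaining 4 are needed. P(none) = 0.51 × 0.3³ = 0.0138. P(one) = 0.49 × 0.027 + 0.51 × 3 × 0.7 × 0.09 = 0.1096. Sensitivity = 1 − 0.1234 = 87.7%.
- Item not counted, so 3 of 4 are needed. 0.51 × 0.343 + 0.49 × 0.784 = 55.9%.

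The same enumeration for all four rules (on vs off):

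| s | 2018 | Revised | MSIS | ICM 2013 |
|---|---|---|---|---|
| 0.5 | 91.8 vs 83.6 | 91.4 vs 78.1 | 40.6 vs 12.5 | 59.4 vs 21.9 |
| 0.7 | 99.3 vs 98.2 | 99.3 vs 96.6 | 78.1 vs 44.2 | 87.7 vs 55.9 |
| 0.9 | 100 vs 100 | 100 vs 100 | 98.7 vs 89.2 | 99.4 vs 92.6 |

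**5. Correlated items.** Assumed positivity in PJI: serum CRP or D-dimer 0.85; ESR, synovial WBC/LE, alpha-defensin and PMN% 0.80; synovial CRP 0.75; histology 0.70; purulence 0.55. Latent correlation 0.2 to 0.5. All PJI patients are treated as culture-entered. Each cell gives correlation 0.2 / 0.5.

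| Criteria | On (%) | Off (%) | Difference | On minus culture at 0.8 |
|---|---|---|---|---|
| 2018 | 98.7 / 94.6 | 96.8 / 91.2 | 1.9 / 3.4 | 0.8 / 1.9 |
| Revised | 98.2 / 93.9 | 94.6 / 88.7 | 3.6 / 5.2 | 1.4 / 2.6 |
| ICM 2013 | 91.1 / 86.3 | 72.0 / 72.1 | 19.1 / 14.2 | 5.2 / 4.7 |
| MSIS | 80.5 / 76.7 | 56.5 / 60.6 | 24.0 / 16.1 | 5.5 / 3.9 |

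The difference column is the item's whole contribution, and also the gap between the two readings of single. The last column compares the forced item with a culture test that is positive in 80% of infected joints; it is closer to the inflation under the at-least-one reading.

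**6. Dilution.** If a fraction f of PJI patients is sinus-only with freely varying cultures, the effect scales roughly by 1 − f. The article does not give f. With an assumed f of 0 to 0.3, 5 points becomes 5 to 3.5.

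**7. Direction.** With the item on, the 2018 definition leads ICM 2013 by 98.7 − 91.1 = 7.6 or 94.6 − 86.3 = 8.3 points. With it off, the lead is 96.8 − 72.0 = 24.8 or 91.2 − 72.1 = 19.1.

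**The case against.** The primary outcome concerns the published minor criteria, and those include a culture item. Setting it to zero at unchanged thresholds turns ICM 2013 into 3 of 4 and MSIS into 4 of 5, which nobody published, and it widens the 2018 definition's lead. This stands: the culture-excluded run should accompany the as-published scoring, not replace it.

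The item rates are assumptions, and with the other items at 0.9 the primary outcome does not move. This also stands. A shift of 1–2 points is 0.6 to 1.2 of 60 patients, small beside the sampling interval above.

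Surgeon unblinding is disclosed in Blind reading of outcomes and again in the Discussion. That is fair. What remains is the contradiction with the double-blind sentence. The Discussion's limitation concerns sample selection for culture and histology; it mentions neither purulence scoring nor the culture overlap.

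None of this removes the overlap. The article itself fixes both the reference standard and the index tests, so the conflict between them is not a detail left to another document.

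**Conclusion.** The overlap holds as a matter of text: following the plan as written gives incorporation bias in the primary sensitivity and in the comparisons. Its existence and the item weights come from the article; its size does not. Under the assumed rates, the inflation against a culture positivity of 0.8 is about 1–2 points (2018 definition), 1–3 (revised), 5 (ICM 2013) and 4–6 (MSIS). The upper limits in that scenario are 2–3, 4–5, 14–19 and 16–24. Under the exactly-one reading, the bias lowers sensitivity instead.

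Stronger readings that the documents do not support:

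- **That the item is a function of group membership for everyone.** Only culture-entered PJI patients are fixed.
- **That the full on/off difference is the bias.** It compares always positive with never counted, and culture would be positive in some infected joints anyway.
- **That the ranking reverses.** In both models, removing culture left no reversal among these four criteria. ICM 2013 does change place with IDSA at s = 0.9 (99.4% with the item, 92.6% without, against 99.0%), but only if IDSA is cut down to histology or purulence, which the article does not define.
- **That the overlap flatters the 2018 definition.** Under the at-least-one reading it helps MSIS and ICM 2013 more. Table 1 is the least affected because of its pre-operative gate.

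**What to change.** 1. In Recruitment and intervention or Statistical analysis, state whether group-defining cultures count towards the single-culture item, and whether single means at least one or exactly one.
2. Beside the as-published scoring, prespecify an analysis of all criteria with the culture item set to zero in both groups and thresholds unchanged. Base any claim about sensitivity independent of the reference standard, or about the best diagnostic method, on both analyses.
3. Add a run with purulence also set to zero.
4. Report how many PJI patients entered on cultures and how many on a sinus tract alone, since that share scales the bias.
5. Reword the double-blind sentence in Study design and objectives to agree with Blind reading of outcomes.

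**Cost.** Re-scoring of data already collected, plus wording. Reported sensitivities will be lower in the culture-excluded run, and MSIS and ICM 2013 are then no longer exactly the published rules, which the report should say.
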